## Abstract

**Background:**

Adolescents with a chronic medical condition (CMC) have an increased risk of developing a substance use (SU) disorder, despite the impact that SU may have on disease-related outcomes. School-based health centers (SBHCs) offer universal screening, brief intervention, and referral for adolescents with chronic medical conditions for substance use treatment. Screening, Brief Intervention, and Referral to Treatment (SBIRT) is an evidence-based early intervention used to detect and address risky substance use that has yet to be broadly adopted in public schools. Moreover, despite extensive research supporting caregiver involvement in treatment for adolescent substance use, SBIRT models that actively engage caregivers are lacking. The primary goal of this qualitative study is the identification of contextual determinants (e.g., barriers and facilitators) of SBHCs implementation potential and adaptation needs of a family-based SBIRT protocol for integration into SBHCs.

**Methods:**

We are conducting this study in two SBHCs within the Chicago Public School system. In these SBHCS we are conducting focus groups with school partners (∼ 30 SBHC staff,∼25 adolescents with chronic medical conditions, and∼25 caregivers). Focus groups will be audio recorded and conducted in English. The semi-structured focus group guides were designed based on the Health Equity Implementation Framework (HEIF) and the Consolidated Framework for Implementation Research (CFIR). We will develop a codebook based on emerging codes from the transcripts and constructs from HEIF and CFIR. Emerging themes will be summarized highlighting similarities and differences between and within the different groups and SBHCs. Descriptive statistics and chi-square tests of associations will be used to assess the distribution of responses on the assessments between the different sites.

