### Aim 1 procedures

In Phase 1 of the focus groups, adolescents with chronic medical conditions (ages 14–18; *n* = 5) with an established medical treatment history at the identified SBHC in Chicago, Illinois, and caregivers (*n* = 5) will be recruited to participate in two separate focus groups developed through CFIR and the HEIF to assist with the refinement of the focus group tools. Due to a long-standing history of disparities in SU treatment and systemic inequities, adolescents with chronic medical conditions living in disinvested areas are likely have significant concerns related to being asked questions about SU in SBHCs. Thus, focus group facilitators will ask questions from the HEIF about perceptions of SU among adolescents with chronic medical conditions and barriers (e.g., confidentiality, stigma, and discipline policies) and facilitators (e.g., peer support and knowledge of treatment options) to SU treatment engagement.

Once feedback from the initial adolescent focus group is incorporated into the HEIF focus group guide, adolescents with chronic medical conditions (ages 14–18; *n* = 10) and caregivers (*n* = 10) from two SBHCs will be recruited to participate in Phase 2 focus groups, with two separate group meetings for each group to evaluate the SBIRT-Family prototype procedures. Focus groups will be conducted at two SBHCs with no more than eight participants per group.

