### Aim 1 analysis

Audio recordings of the focus group sessions will be transcribed verbatim and uploaded into Dedoose, a qualitative data analysis platform that supports mixed-methods research. Qualitative data from the focus groups and quantitative data from self-report measures will be analyzed using a convergent mixed-methods design. Constructs from CFIR and HEIF will guide qualitative coding and interpretation. An initial codebook will be developed through a combination of deductive codes derived from CFIR and HEIF domains and inductive codes emerging from the transcripts and focus group guides. After iterative discussions and pilot coding to ensure consistency and consensus, the full dataset will be double-coded by trained team members. Interrater reliability will be assessed using pooled Cohen's kappa, and discrepancies will be resolved through team discussion. Quantitative survey data (e.g., demographic characteristics) will be analyzed using descriptive statistics to provide contextual information about the focus group participants. Frequencies, means, and standard deviations will be reported, and data will be stratified by partner group (e.g., adolescents, caregivers). Following separate analysis of qualitative and quantitative datasets, findings will be integrated using a joint display matrix to identify areas of convergence, complementarity, or divergence across data sources. This approach will allow us to compare and contrast themes across participant groups and assess how survey responses align or diverge from qualitative perspectives. Emerging themes that fall outside CFIR and HEIF constructs will be documented as new insights and may inform updates to existing implementation frameworks.

Aim 2: Engage with SBHC Staff to Identify Contextual Determinants of SBIRT-Family integration into clinic workflows using CFIR and HEIF.

SBHC staff recruited for focus groups will complete organizational assessments (e.g., observational studies of clinic workflows). The PI will clarify organizational readiness for implementing SBIRT-Family procedures and identify optimal workflows to engage adolescent patients around and within SBHC clinic appointments.

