### Aim 2 analysis

Mixed-methods analyses will be conducted using data collected from qualitative (e.g., workflow observations, co-design workshops) and quantitative sources (e.g., observation duration, feasibility, and acceptability ratings). A convergent parallel design will be employed to synthesize qualitative and quantitative data concurrently.

Quantitative data, including self-report scores from the Acceptability of Intervention Measure (AIM), Intervention Appropriateness Measure (IAM), and Feasibility of Intervention Measure (FIM), will be analyzed using descriptive statistics (means, SDs, and item-level distributions) (see Table 2). These data will help quantify SBHC staff's perceptions of the caregiver-adapted SBIRT model and highlight preliminary feasibility considerations. While these measures are widely used and validated in implementation research, they are known to exhibit ceiling effects, particularly in early-stage acceptability testing which may limit variability and sensitivity to subtle differences in staff perspectives. To address this limitation, item-level response distributions will be examined alongside means and standard deviations to detect any skewness or clustering of responses. Quantitative data from the workflow observations will be summarized using frequency counts and average durations for key tasks to inform the logistical feasibility of implementation.

Qualitative data from observational field notes and co-design sessions will be analyzed using thematic analysis, guided by CFIR and HEIF. Community partner suggestions regarding implementation processes, potential barriers, and delivery preferences will be coded and synthesized. As in Aim 1, deductive and inductive approaches will be used to capture both framework-aligned and new insights.

Following individual analyses, qualitative and quantitative findings will be compared and organized into a joint display matrix. This will facilitate integration of SBHC staff's narrative perspectives with numeric ratings and observational data. Integrated findings will be used to develop an initial implementation plan, including a short list of candidate implementation strategies tailored to the SBHC context. These strategies will inform the design of a future multi-site hybrid trial.

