## Discussion

Adolescents with chronic medical conditions have high rates of risky drinking and drug use. Yet, they are not routinely screened for SU in SBHCs even though they frequently interact with the healthcare system for management of their chronic medical conditions, highlighting a major missed opportunity. This research protocol will facilitate the implementation of family-focused SBIRT procedures in SBHCs within the third largest public-school system in the country (66).

Implementation of an evidence-based substance use approach in SBHCs for adolescents with chronic medical conditions requires a thorough understanding of context-specific bottlenecks, factors that contribute to workflow integration, and predictors of SBHC staff adoption to protect as many adolescents with chronic medical conditions as possible from risky alcohol use and substance use that can lead to future dependence, overdose, or accidental death. Findings from this study will generate insights on implementation determinants that affect SBIRT-family implementation in SBHCs from the perspective of a diverse group of community members and SBHC staff at different levels of the organization in Chicago Public Schools. A variety of factors between and within settings and other key characteristics of participants (race and ethnicity, gender identity, location, role in the community, etc.) is expected to be prominent (67–70). In addition, the acceptability of the adapted intervention and the implementation plan may vary depending on participants’ awareness of existing evidence of brief family-focused substance use interventions (71, 72) and their status within the SBHC system. Given recent CPS initiatives to integrate substance use prevention and intervention into their programming, we do not expect measures of acceptability, appropriateness, and feasibility to vary among SBHC staff based on demographic characteristics.

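### The abstract plans chi-square tests between the two sites that the analysis sections do not carry and that the body's Phase 2 group sizes cannot support

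*Protocol article*

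**What the plan says.** The Methods paragraph of the abstract gives the only significance test in the article: "Descriptive statistics and chi-square tests of associations will be used to assess the distribution of responses on the assessments between the different sites". It also gives the sample as about 30 staff, "25 adolescents with chronic medical conditions, and∼25 caregivers", recruited in two centers.

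The body differs on both counts.

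- **Analysis.** For the survey data, Aim 1 analysis says: "Frequencies, means, and standard deviations will be reported, and data will be stratified by partner group (e.g., adolescents, caregivers". Site is not mentioned there. In Aim 2 analysis, the acceptability, appropriateness and feasibility scores "will be analyzed using descriptive statistics (means, SDs, and item-level distributions". Neither section names a test or a quantitative comparison by site.
- **Group sizes.** Aim 1 procedures has 5 adolescents and 5 caregivers in Phase 1. It then has 10 adolescents "and caregivers (*n* = 10) from two SBHCs will be recruited to participate in Phase 2 focus groups". Aim 2 procedure has 5 staff from one center in Phase 1 and 16 staff over two centers in Phase 2. The split between the centers is not stated.

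**The concern.** The article gives two accounts of the quantitative analysis. One tests for differences between sites; the other describes responses by group. A reader cannot tell which will be done, and the difference matters at these sample sizes. With a handful of people per site, the choice between an ordinary and an exact test can decide whether a site difference is declared. A non-significant result says almost nothing about whether the two sites are alike. The results are meant to inform an implementation plan and a later trial, so a site p-value of either kind could be given weight it does not have.

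**Working it through.** **1. Group sizes, abstract against body.**

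| Group | Phase 1 + Phase 2 | Sum | Abstract |
|---|---|---|---|
| Adolescents | 5 + 10 | 15 | about 25 |
| Caregivers | 5 + 10 | 15 | about 25 |
| Staff | 5 + 16 | 21 | about 30 |

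None of the abstract's totals is reproduced. Reading the Phase 2 numbers as per center gives 5 + 20 = 25 for adolescents and caregivers, which matches. The same reading gives 5 + 32 = 37 for staff, which does not.

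**2. Expected counts.** The four expected counts of a 2x2 table add up to N. If each is at least 5, N is at least 20. Phase 2 has N = 10, 10 and 16 within the groups, so the usual condition fails under any split between sites. With an even split (assumed), the best attainable minimum is the number per site x 0.5: 5 x 0.5 = 2.5 for adolescents or caregivers, and 8 x 0.5 = 4.0 for staff.

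**3. True size of the uncorrected Pearson test.** The level is not stated, so two-sided 0.05 is assumed. For a common response probability p, the size is the sum, over all tables with Pearson p-value of at most 0.05, of Bin(a; n, p) x Bin(b; n, p).

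| Per site | p = 0.5 | p = 0.8 | p = 0.9 | Maximum over p |
|---|---|---|---|---|
| 5 v 5 | 6.1% | 3.8% | 1.0% | 6.2% |
| 8 v 8 | 7.7% | 2.7% | 0.5% | 7.7% |

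The test is somewhat liberal near the middle of the scale and conservative where most people agree.

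**4. One table, two answers.** At 5 v 5, a result of 5/5 against 2/5 gives Pearson p = 0.038 and Fisher p = 0.167.

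**5. Power of Fisher's exact test**, for an 80% v 40% difference (an illustrative contrast, not in the documents): 14% at 5 v 5 and 24% at 8 v 8. By the normal approximation, about 23 per site would be needed for 80% power.

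**6. The same checks at the abstract's totals.** An even split gives about 12 v 13 and 15 v 15. The best minimum expected counts are 5.76 and 7.5, and the maximum Pearson size is 5.3% and 5.5%. Fisher power for 80% v 40% is 50% and 45%. If 80% endorse an item (assumed; Aim 2 analysis does expect ceiling effects), the minimum expected counts drop to 12 x 0.2 = 2.4 and 15 x 0.2 = 3.0.

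**The case against.** The strongest reply is that little harm follows. The study is qualitative. Strategies come from coded focus-group material, a matching tool and review with staff, and no stated decision turns on a site p-value. The abstract's own totals would give 12 to 15 per site, where the test behaves acceptably. The abstract does not say that each partner group is tested separately. Pooling all three groups in Phase 2 would give 18 v 18 (5 + 5 + 8 per site) and a best minimum expected count of 9.0. Data collection may also extend until saturation.

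Most of this stands, and it sets the severity. It does not remove the point. The abstract's totals disagree with the body, and pooling adolescents, caregivers and staff is not described anywhere. Extension to saturation fixes no number.

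Several stronger readings are tempting, and the documents do not support them.

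- *The chi-square test is invalid here.* Its size is 6% to 8% at worst in 2x2 tables and under 5% at high endorsement. For items with five response options (an assumption, since Table 2 gives none), simulation put it at about 2% to 4%. Unreliable and weakly informative is the accurate description.
- *Item-by-item testing will yield a countable number of false positives.* No section plans item-level tests; item distributions are used descriptively.
- *Site will be confounded with phase.* No section pools Phase 1 and Phase 2 survey data. Phase 1 is there to refine the focus-group tools.
- *The Discussion draws a conclusion from a null test.* The statement that "we do not expect measures of acceptability, appropriateness, and feasibility to vary among SBHC staff based on demographic characteristics" is a prior expectation with a reason given. It concerns demographics, not site.

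**Conclusion.** The point holds as a minor one. The abstract promises a between-site test that the two analysis sections do not carry. On the body's Phase 2 counts, the usual expected-count condition cannot be met within any partner group, whatever the split. With an even split and a two-sided 5% level (both assumed), the uncorrected test has a true size of up to 6% to 8% and an exact test has 14% to 24% power for an assumed 80% v 40% difference. The first result needs only the stated counts and testing within groups; the others also rest on these assumptions. If the abstract's totals prove to be the right ones, the size problem largely goes, but power stays at about 50% or less for the same contrast.

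**What to change.** 1. Reconcile the group sizes in the abstract with those in Aim 1 procedures and Aim 2 procedure, and state whether the Phase 2 numbers are totals or per center.
2. Delete the chi-square clause and report counts and item distributions by partner group and site. Alternatively, put a test into the analysis sections: Fisher's exact test for binary responses or an exact rank test for ordinal ones, on named scale totals, labelled exploratory.
3. State that a non-significant result will not be read as similarity between the sites.
4. Do not substitute bootstrap intervals at 5 to 8 per site. In a simulation with normal data, nominal 95% percentile intervals for a mean difference covered only about 89% to 90%.

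The change is to wording only. Under the first option in step 2, the study gives up site p-values that its numbers could not support.

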**Discussion:**

This study will describe key implementation determinants and SBIRT-Family adaptation needs from the perspective of multiple end-users. Results will provide insights for a randomized pilot hybrid type 2 effectiveness implementation study of the adapted SBIRT-Family model in two SBHCs assessing effectiveness outcomes (SU and linkage to treatment) and implementation outcomes (reach, adoption, equity, and cost). This research protocol will provide formative data to inform the development of a highly scalable approach that can be used in SBHCs across the country to serve a vulnerable population of adolescents with chronic medical conditions.

## Introduction

Adolescents with a chronic medical condition have been reported to be at increased risk for developing a substance use (SU) disorder. For instance, adolescents with chronic medical conditions are more likely to misuse alcohol, cannabis, and nicotine and initiate SU at younger ages compared to adolescents without chronic medical conditions (1–3). Importantly, engaging in SU may have an impact on their disease-related outcomes. SU in this population has implications for academic (engagement, grades, attendance), behavioral health (e.g., anxiety, depression, traumatic stress) and medical health outcomes (e.g., problematic medication interactions, treatment non-adherence, and poor disease management) (3).

In the United States, adolescents with chronic medical conditions such as asthma, diabetes, sickle cell, epilepsy, and cystic fibrosis, account for the bulk of pediatric ED visits and inpatient hospitalizations (4, 5). While inpatient hospitalizations provide acute medical management, many adolescents receive ongoing care in outpatient settings particularly in integrated primary care systems in community settings such as school-based health centers (SBHCs) (2). SBHCs are a nationally recognized model of care delivery that provide children, adolescents, and caregivers with accessible, comprehensive health services, directly within school environments. These centers are often staffed by interdisciplinary teams, including nurse practitioners, physicians, social workers, and behavioral health specialists, and offer services ranging from physical exams and immunizations to mental health counseling and chronic condition management (6). SBHCs exist across diverse educational settings in the United States and are especially common in schools serving historically underserved populations. Their purpose is to reduce barriers to care by eliminating logistical challenges such as transportation, missed school, or lack of parental availability. Nationally, more than 2,500 SBHCs serve nearly 6.3 million students annually, with funding and policy oversight varying by state (7).

In our specific study setting—a large urban SBHC network in the Midwest—SBHCs are embedded in schools and managed through collaborative partnerships between the school district and a mix of federally qualified health systems and hospital-affiliated health centers. Federally qualified health centers are community-based organizations that receive federal funding under Section 330 of the Public Health Service Act and are required to provide comprehensive care to medically underserved populations, often on a sliding scale (8). In contrast, hospital-affiliated health centers are operated by academic medical centers and offer integrated specialty care and have greater access to institutional resources, training, and research infrastructure (see Table 1).

**Table 1 T1:** Comparison of SBHC models and local study context.

Model infrastructure components	FQHC-sponsored SBHCs	Hospital-affiliated SBHCs	Local study context
Funding	Federally funded	Institutional or hospital funding	Hospital-funded project in partnership with local school district and FQHCs
Target population	Medically underserved communities	Medically complex populations	Youth with chronic conditions
Governance	Community-based board	Hospital or academic oversight	Administered by hospital with collaboration from school district partners and FQHCs
Scope of services	Comprehensive	Comprehensive	Preventive care, chronic disease management, behavioral health
Integration with specialty care	Typically limited	High integration (e.g., shared EHRs)	Close collaboration with pediatric subspecialists
Staffing model	PCPs, behavioral health clinicians, RNs, MAs	PCPs, behavioral health clinicians, RNs, MAs	PCPs, behavioral health clinicians, RNs, MAs
SBIRT implementation status	Variable; often limited adoption	Not widely implemented or adapted for chronic conditions	Behavioral health screening in place; SBIRT not yet formally implemented or adapted

Many adolescents with chronic medical conditions are often prescribed pain medications to address pain control related to their conditions. Clinicians in pediatric treatment settings such as SBHCs are therefore faced with the challenge of appropriately addressing pain control, while preventing and addressing opioid misuse among adolescents with chronic medical conditions in the current climate of the opioid misuse epidemic (9). Clinicians in SBHCs also must be poised to address behavioral health concerns such as SU—behavioral health concerns are the focus of a large proportion of visits in SBHCs. Having access to SBHCs increases the likelihood of adolescents receiving services to address these concerns (10–12). Therefore, SBHCs offer a unique setting to address and prevent the escalation of SU in adolescents with chronic medical conditions (13).

Screening, Brief Intervention, and Referral to Treatment (SBIRT) for adolescents is an evidence-based approach to prevent and address risky SU (13, 14). The goal of the SBIRT model is to employ universal screening using a validated tool [e.g., Screening to Brief Intervention (S2BI)] (15, 16) to identify adolescents at risk of SU disorders, administer appropriate brief intervention such as motivational interviewing, and initiate referral to treatment (17, 18). SBIRT is widely endorsed as a universal strategy for detection and early intervention of SU and is recommended as a part of routine care in a variety of settings (13). Implementation of SBIRT in SBHCs has been associated with reductions in alcohol and cannabis use among adolescents but has not yet been widely adopted (6, 10, 11). SBHCs present a unique opportunity to adapt SBIRT for adolescents with chronic medical conditions to address modifiable SU risk, improve academic outcomes, and reduce related disease burden.

Standard SBIRT models, both within and beyond SBHCs, focus almost exclusively on the adolescent by including only the adolescent in the screening, intervention, and referral processes (12, 13). Yet, evidence indicates a need for major improvements in SBIRT engagement, effectiveness, and feasibility for adolescents in this setting (19–21). Involving caregivers (e.g., biological parents or legal guardians) could enhance the effectiveness of each phase of the SBIRT process by broadening the approach, as caregivers are vital sources of information regarding adolescent SU and mental health. During the screening phase, the use of multiple sources of information has been shown to be more accurate than relying on a single source for adolescent SU (22, 23). Proactively incorporating caregivers in the screening process for adolescent SU may be helpful to increase the likelihood of detection when youth have minimized self-report (24, 25). Pertaining to the BI phase, BIs for adolescent SU that incorporate parents have shown preliminary effectiveness (26, 27) and are likely to have considerable added value over adolescent-only BIs (28). Notably for this population, caregivers of adolescents with chronic medical conditions who have behavioral health concerns for their children often seek guidance from health clinicians (29). BIs can also help caregivers to learn effective parenting strategies (e.g., communication, coping, problem solving) that have been shown to reduce the risk of adolescent SU (30) and that are likely to be especially important for adolescents with chronic medical conditions who have special healthcare needs. Such caregiver strategies are likely to be especially important for adolescents with chronic medical conditions whose caregivers are likely to communicate with SBHC staff more extensively than caregivers of adolescents without chronic medical conditions. Regarding RT, influencing adolescents to enroll in SU services typically requires family involvement (28, 31). SBHC clinicians are well positioned to shape caregiver attitudes towards treatment options given their authority on healthcare issues (28, 29, 31).

Although SBIRT is widely endorsed, it is underutilized in SBHC settings, it has limited effectiveness, and questions remain about optimal SBIRT delivery strategies in SBHCs (17, 32, 33), particularly for adolescents with chronic medical conditions. Moreover, even though research strongly supports involving caregivers in treatment for adolescent SU (34–37), SBIRT models that actively engage caregivers are lacking. These limitations highlight the need for comprehensive evidence from school partners (e.g., SBHC staff, adolescents, and caregivers) on factors that will facilitate or impede the delivery and uptake of SBIRT in SBHCs for adolescents with chronic medical conditions. The primary goal of the current qualitative study is the identification of key contextual determinants (e.g., barriers and facilitators) to inform the selection of implementation strategies of a caregiver adapted SBIRT on substance use for adolescents with CMC receiving care in SBHCs.

This study is poised to advance research on SBIRT delivered in SBHCs in four primary ways. First, the standard SBIRT approach implemented in other state SBHCs focuses almost exclusively on the general adolescent population and not specifically on adolescents with chronic medical conditions. Second, conventional SBIRT targets adolescents only, without caregiver involvement, in screening and intervention procedures (13, 38). Third, while best practices for integration of SBIRT in SBHCs are emerging (38), implementation remains low nationally (13). Lastly, more research is needed to understand how family-focused SBIRT implementation determinants in SBHCs impact SU outcomes for adolescents with chronic medical conditions.

